## Discussion

### Expected Findings

As the COVID-19 pandemic ceases, more patients enter the chronic phase of the disease. Identifying groups at high risk of cognitive and psychiatric dysfunction may allow for targeted intervention to effectively meet their physical, neurological, and psychological health care needs. Our study, conducted in the aftermath of the COVID-19 pandemic, provides a unique opportunity to investigate the persisting health effects of the virus on those who have recovered from the acute phase of the disease. We specifically aim to explore post–COVID-19 fatigue and mental health disorders using specific tools to separate physical and psychological fatigue symptoms. We also use a prospective cohort multicenter study design, which is less prone to bias, and we aim to include both hospitalized and nonhospitalized patients, covering all degrees of acute COVID-19 severity. We anticipate that our research will reveal a significant association between the presence and severity of mental health symptoms, including depression, anxiety, and PTSD, and the degree of physical and psychological fatigue in patients following COVID-19. We expect to observe that patients experiencing more pronounced mental symptoms will report higher levels of physical and psychological fatigue.

The potential links between mental symptoms and fatigue suggest a connection between the mental well-being of patients post COVID-19 and their experience of fatigue, encompassing both physical and psychological dimensions. The existing research has indicated a high prevalence of anxiety and depression symptoms among patients hospitalized with COVID-19 infection, with a quarter of patients experiencing at least mild symptoms of acute stress disorder [42]. Moreover, a study conducted in Iran after the outbreak of COVID-19 found a correlation between the prevalence of chronic fatigue syndrome and PTSD [45]. The study reported that 5.8% of subjects experienced PTSD symptoms 6 months after the onset of SARS-CoV-2 infection. Interestingly, the study also noted that female sex was associated with a higher risk of fatigue. At the same time, variables such as oxygen saturation at admission, primary symptoms, ICU admission, and laboratory test parameters did not show a significant association with fatigue occurrence.

Based on these findings, we anticipate that patients post COVID-19 may exhibit more pronounced symptoms of depression and anxiety and heightened levels of physical and psychological fatigue. This insight emphasizes the importance of considering mental health as a crucial factor in understanding the long-term effects of COVID-19. It underscores that the impact of the virus extends beyond the acute illness phase and can manifest in persistent mental symptoms that influence patients’ overall well-being. Moreover, it can imply that addressing anxiety symptoms in post–COVID-19 care may have a positive impact on reducing fatigue and improving patients’ quality of life. We also aim to explore the prevalence and severity of PTSD symptoms in a subset of patients following COVID-19. While this is not the primary focus of our research, assessing the presence of PTSD symptoms in this study population allows for a better characterization of the patient group. Some participants continue to experience PTSD symptoms following COVID-19 infection, suggesting that the psychological impact of the virus can be long-lasting. These findings may shed light on the need for comprehensive mental health support for patients post COVID-19.

The implications of our potential findings are widespread. They underscore the importance of integrated care for patients post COVID-19 that addresses both physical and mental health aspects. Clinicians and health care providers will then be aware of the potential for persistent mental symptoms and their impact on patients’ fatigue levels and overall HRQoL.

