**Methods:**

Using a consecutive nonrandom sampling technique, we will conduct a prospective cohort multicenter observational study in 5 Portuguese hospitals. Symptomatic adult patients with previous COVID-19 attending follow-up consultations will be enrolled. We will include patients who had mild, moderate, and severe acute disease. We will assess clinical outcomes related to COVID-19, including the type of respiratory support such as high-flow nasal cannula, noninvasive ventilation, and invasive mechanical ventilation. The exclusion criteria will include previous severe psychiatric disorders confirmed by a psychiatrist; refusal or inability to respond to the questionnaire; concomitant neurological disorder; persistent fatigue symptoms during the 6 months before infection; and the need for invasive mechanical ventilation during COVID-19 infection due to a high prevalence of postintensive care syndrome. Our primary outcome is the prevalence of fatigue in patients with post–COVID-19 depression and/or anxiety, as measured by the Chalder Fatigue Scale (CFQ-11) and the Hospital Anxiety and Depression Scale (HADS). The secondary outcomes will include an assessment of health-related quality of life via the EQ-5D questionnaire and an exploration of the prevalence of symptoms of posttraumatic stress disorder (PTSD) using the 14-item Posttraumatic Stress Scale (PTSS-14). We will also examine the association between mental health symptoms and the severity of acute COVID-19. The post–COVID-19 data will be collected at least 6 months after the positive test and no longer than 9 months during the clinical appointment.

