Research questions of the study.Research Question 1 (primary outcome):Do patients with long COVID who experience depression and/or anxiety symptoms have a higher prevalence of fatigue?Research questions 2 to 4 (secondary outcomes):Is there a correlation between the type of fatigue and depression and/or anxiety symptoms among patients post COVID-19?Is there a correlation between fatigue and the presence of PTSD symptoms in patients post COVID-19?Do patients with fatigue associated with mental health disorders have a lower health-related quality of life (HRQoL) after COVID-19?

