### Secondary Outcomes

#### Depression and Anxiety

Symptoms of depression and anxiety will be assessed using the HADS [27], a practical, validated tool for assessing symptom severity in anxiety and somatic disorders in psychiatric and primary care settings and the general population [32]. This measure comprises 14 items, 7 measuring symptoms of anxiety and 7 measuring symptoms of depression. The scores are categorized into different ranges: 0 to 7 as “normal,” 8 to 10 as “mild,” 11 to 14 as “moderate,” and 15 to 21 as “severe.” The HADS questionnaire has been validated in many different languages and settings [32-34].

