The 5 phases of the statistical analyses carried out in this study.Phase 1: Characterization of the patient sample1.1. Sociodemographic analysis of the variables collected at T1 and the variables from the surveyed instruments at T2. This involves descriptive analysis, both univariate and bivariate, which will be differentiated by:1.1.1. Quantitative variables: mean and SD, coefficient of variation, and median and IQR1.1.2. Qualitative variables (nominal and ordinal categorical): analysis of distributions through absolute and relative frequencies, including absolute and relative accumulated frequencies1.1.3. Quantitative variables will be reported alongside appropriate tests for normal distribution to ensure the accuracy and validity of our statistical analyses.1.2. Bivariate and descriptive analysis using 2D tables will be calculated for all qualitative variables belonging to T1 with all instrument scores collected at T2: Chalder Fatigue Scale (CFQ-11), Hospital Anxiety and Depression Scale (HADS), 14-item Posttraumatic Stress Scale (PTSS-14) adapted to COVID -19, and EQ- 5D plus recorded COVID-19 symptoms. The previous points will be reiterated in this bivariate context, utilizing the computational aid of split->file categorical variables in situations where one variable is metric and the other is categorical.1.3. Internal consistency and reliability analysis of the T2 instruments: calculation of the Cronbach alpha (general and partial) for all ordinal items and item subgroups differentiated by the subscales defined by the respective authorsPhase 2: Determination of fatigue incidence caused by long COVID and its relationship with T1 and T2 variables2.1. Procedures for determining fatigue cutoff points in this cohort of patients:2.1.1. Bivariate analysis using optimal binning procedures for categorical variables (age class, sex, and BMI) with the total fatigue score, as well as partial scores of physical and psychological fatigue2.1.2. Multivariate analysis by constructing models in the format of decision trees via the CHAID (chi-square automatic interaction detection) algorithm [41], with total and partial fatigue scores as dependent variables2.2. Inferential analysis based on variables resulting from 2.1.1 and/or 2.1.2, considering the complexity of variables in T1 and T2:2.2.1. (1) Chi-Square tests to capture the association of categorical variables; (2) Shapiro-Wilk tests to verify the distribution of quantitative variables; (3) tests for comparing 2 or more population means: parametric analysis of variance (ANOVA) test and nonparametric (Kruskal-Wallis) test; and (4) correlation tests (Spearman or Pearson) to verify the degree of association between T2 instrument scalesPhase 3: Determination of patient groups based on fatigue differentiation3.1. Conducting classification analysis using clustering techniques, specifically the 2-step cluster analysis, to explore variables with greater power in differentiating groups of patientsPhase 4: Exploration of the best combination of T1 and T2 variables capable of discriminating patient fatigue levels through a discriminant multivariate analysisPhase 5: Investigation of the association between phase 3 groups and all T2 instrument scales using chi-square association tests

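### With depression and anxiety pooled and no named analysis estimating one given the other, the plan cannot support its suggestion that addressing anxiety may reduce fatigue

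*Protocol article*

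**What the plan says.** **Exposure.** Research Question 1 in Textbox 1 asks: "Do patients with long COVID who experience depression and/or anxiety symptoms have a higher prevalence of fatigue". The abstract gives the primary outcome as "the prevalence of fatigue in patients with post–COVID-19 depression and/or anxiety". The question on fatigue type keeps the same pooling: "Is there a correlation between the type of fatigue and depression and/or anxiety symptoms among patients post COVID-19". Power and Sample Size also uses a single split, 100 patients with adverse mental health symptoms and 100 without.

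**Measurement.** Depression and Anxiety, under Secondary Outcomes, describes the HADS: "This measure comprises 14 items, 7 measuring symptoms of anxiety and 7 measuring symptoms of depression". Separate subscale scores are therefore available. Data Collection places both the HADS and the CFQ-11 at the second visit (T2, 6 months).

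**Analysis.** Textbox 2, step 2.2.1, lists chi-square tests, comparisons of means (ANOVA or Kruskal-Wallis) and Spearman or Pearson correlations between the T2 scales. Step 2.1.2 adds "Multivariate analysis by constructing models in the format of decision trees via the CHAID" algorithm, with total and partial fatigue scores as dependent variables. Phase 4 looks for the combination of T1 and T2 variables that best discriminates fatigue levels, by discriminant analysis.

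**Inference.** Expected Findings says the anticipated result can imply that "addressing anxiety symptoms in post–COVID-19 care may have a positive impact on reducing fatigue".

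**The concern.** A pooled exposure cannot show which of its two components carries a difference in fatigue. A correlation of one subscale with fatigue, taken alone, cannot show it either: if anxiety and depression scores are correlated, anxiety will correlate with fatigue even when only depression has a link of its own. Yet the one sentence that turns the expected results into a message about care names anxiety alone.

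The sentence also concerns what would happen if anxiety were addressed. That is a statement about the effect of an action, drawn from two questionnaires completed at one visit.

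At stake is what the study may conclude, not its primary result. The Results section says the links can guide targeted interventions, so it matters whether a link belongs to anxiety, to depression or to both. The data needed to separate them are already being collected.

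**Working it through.** **1. Can any named analysis supply an anxiety association given depression?**

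| Step | Can both HADS subscales enter? | Does it estimate anxiety given depression? |
|---|---|---|
| 2.2.1, tests and correlations | No, two variables at a time | No |
| 2.1.2, CHAID trees | Possibly; predictors are not named | No; it splits the sample on selected variables, within the step that derives fatigue cutoffs |
| Phase 3 and Phase 5, clusters and chi-square tests | Clusters possibly | No; it groups patients, then tests associations with the groups |
| Phase 4, discriminant analysis | Yes, HADS is a T2 instrument | Not specified to; it seeks a best-discriminating combination, and with correlated predictors may keep one subscale and drop the other |

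**2. How easily could depression alone produce an anxiety correlation?** The documents give no figure to reproduce here and none of the correlations needed, so this is an illustration on assumptions.

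Inputs:
- n = 187: the target of 250 less the projected 25% loss, 250 × 0.75 = 187.5, rounded down.
- Two-sided 5% level. The protocol gives .05 without stating sidedness.
- Assumed: depression–fatigue correlation 0.3 to 0.5; HADS subscale correlation 0.5 to 0.7; no link of anxiety with fatigue beyond depression.

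Formulas: under the last assumption, r(anxiety, fatigue) = r(anxiety, depression) × r(depression, fatigue). The probability of significance by Fisher's z is Φ(atanh(r) × √(n − 3) − 1.96), with √184 = 13.565.

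Central case: r = 0.6 × 0.4 = 0.24; atanh(0.24) = 0.2448; 0.2448 × 13.565 = 3.32; Φ(3.32 − 1.96) = 0.91. A simulation of the same case (4,000 runs) gave 91.9%.

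| Subscale r | Depression–fatigue 0.3 | 0.4 | 0.5 |
|---|---|---|---|
| 0.5 | r = 0.15, 54% | r = 0.20, 79% | r = 0.25, 93% |
| 0.6 | r = 0.18, 69% | r = 0.24, 91% | r = 0.30, 99% |
| 0.7 | r = 0.21, 82% | r = 0.28, 97% | r = 0.35, over 99% |

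At the planned analysis size of 200 the central case is 93%.

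**3. What does a joint model do?** With both subscales entered and measured without error, the anxiety term is significant in 5% of studies in the central case, which is the nominal level. Measurement error weakens this. Keep the observed correlations at 0.6 and 0.4 and assume reliability 0.8 for each subscale:
- error-free subscale correlation: 0.6 / 0.8 = 0.75
- error-free depression with fatigue: 0.4 / √0.8 = 0.447
- observed anxiety with fatigue: 0.75 × 0.447 × √0.8 = 0.30
- partial r = (0.30 − 0.6 × 0.4) / √[(1 − 0.4²)(1 − 0.6²)] = 0.06 / 0.733 = 0.082
- atanh(0.082) × √(187 − 4) = 1.11, so the term is significant in about 20% of studies

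At reliability 0.9 the same steps give about 8%.

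**4. Is a joint model feasible at this size?** Assume both marginal correlations with fatigue are 0.4. The partial correlation of anxiety given depression at N = 200 is then 0.25, 0.22 and 0.18 for subscale correlations of 0.5, 0.6 and 0.7, with power 0.95, 0.87 and 0.74. At a subscale correlation of 0.8 power falls to 0.54. If anxiety has the weaker marginal link (0.4 against 0.5 for depression), power at a subscale correlation of 0.6 is 0.53.

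**5. Timing.** HADS and CFQ-11 are both T2 instruments and the study assigns no treatment. A coefficient from step 3, however well adjusted, is a same-visit association. It does not show which came first or what would follow from changing anxiety.

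**The case against.** **The pooling is deliberate.** No research question asks which of the two symptoms drives fatigue, so a pooled group answers what is asked. This stands: the pooled primary question is not an error and should stay. The difficulty arises only where an anxiety-specific statement is built on it.

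**The plan is not limited to pairwise work.** A reader might infer that each HADS scale is only ever correlated with fatigue one at a time. The documents do not support that: the CHAID trees and the discriminant analysis are multivariable and may include both subscales. What remains is narrower. Neither is specified to give the anxiety association given depression.

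**The sentence is hedged.** It says the result can imply something that may happen, it sits under Expected Findings, and the abstract and conclusion carry no anxiety-only message. A reader might call it the study's intended message; the text does not bear that weight. The hedge does not supply an analysis to support it.

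**The percentages are a chosen scenario.** This is correct. In that scenario the anxiety–fatigue correlation is truly non-zero, so rejecting zero is a right answer to a question about correlation. It misleads only if read as an independent or causal link. A joint model is also no complete cure when subscales are measured with error, as the 20% figure shows.

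**An analysis plan not shown may name such a model.** It may. But the article sets out all five phases, and the conflict is between those phases and an inference printed in the same article. Nor could any added model justify a claim about the effect of addressing anxiety.

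**Conclusion.** The point holds as a limit on what may be concluded. The primary comparison is unaffected. As described, the plan pools depression and anxiety, names no analysis that estimates one association given the other, and then suggests a benefit from addressing anxiety. Two things stand against that sentence: a marginal anxiety correlation may be carried by depression, and a same-visit association without an intervention says nothing about the effect of treatment. The second is the stronger objection and rests on no assumed number.

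The range of about 54% to over 99% shows that the first problem could be common. It depends wholly on assumed correlations and on anxiety having no link of its own. It does not predict what this cohort will show, and it is no evidence that anxiety is unrelated to fatigue.

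The change should be made: it is cheap, uses data already collected and alters what the study can say.

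**What to change.** 1. Keep the pooled depression and/or anxiety group for Research Question 1.
2. Add to Textbox 2 one named model for each CFQ-11 score (total, physical, psychological), with the HADS-anxiety and HADS-depression scores entered together as continuous variables. Base any statement specific to anxiety or to depression on its coefficient given the other, reported with its interval. State that measurement error in the subscales leaves some residual confounding.
3. Reword the sentence in Expected Findings as an association, either adjusted for the other subscale or with depression and/or anxiety symptoms jointly. Remove the implication that treating anxiety reduces fatigue.

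**Cost.** One model form fitted to three scores, and one sentence; no new data. The intervals widen because the subscales are correlated: by the factor 1/√(1 − r²), the standard error grows by about 15%, 25% and 40% for subscale correlations of 0.5, 0.6 and 0.7. If they correlate very highly, the data may not separate the two, and the report should then say so.

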### Limitations

Our study’s limitations include the possibility of sampling bias, as individuals with more severe symptoms of fatigue or other mental health symptoms may be less likely to participate. This possibility could result in underrepresentation and bias within the study’s findings. To minimize this, we will use diverse recruitment methods across multiple sites and collect data on participants’ reasons for declining participation. We will also provide detailed information about the study and its potential benefits to participants while ensuring an ethical and respectful recruitment process sensitive to participants’ health concerns and symptoms.

We also acknowledge the limitations related to our exclusion criteria and use of the CFQ-11, which has yet to undergo specific validation for patients with COVID-19. This recognition underscores the importance of future research endeavors to validate the applicability of the CFQ-11 within this patient population, despite its utilization in prior studies [46-48].

While there are valid concerns regarding the exclusion criteria and assessment of psychiatric disorders in our study—including the fact that assessing preexisting fatigue may be difficult—we have devised a plan to mitigate these concerns. We intend to meticulously collect detailed medical histories and review the medical records of all enrolled patients to ensure the precise application of the exclusion criteria. However, a notable limitation of our study arises from the absence of a baseline assessment conducted before the onset of COVID-19 infection. This absence impedes our ability to comprehensively evaluate the influence of COVID-19 on various health parameters, such as fatigue and mental health. The absence of a baseline assessment may also limit our capacity to distinguish between preexisting conditions and post–COVID-19 effects, which is a key consideration in understanding the full spectrum of the virus’s impact on individuals. Additionally, while we acknowledge that the measurements used in the study are based on self-report—and therefore subjective—we emphasize that self-reported questionnaires are commonly used in scientific studies. These questionnaires hold significance in assessing the extent of physical and psychological fatigue in patients following COVID-19. Despite these limitations, our study is poised to make a significant contribution to the existing literature by shedding light on the impact of COVID-19 on mental health. This research has the potential to guide future treatment and management strategies, serving as a valuable resource for the health care community.

### Conclusion

This study protocol outlines a critical investigation into the lingering physical and psychological effects of long COVID. It emphasizes the importance of understanding the ongoing health challenges individuals face even after recovering from the acute phase of the virus. This study’s research questions focus on assessing the potential correlations of mental illness symptoms (ie, physical and psychological fatigue) among patients post COVID-19.

In the aftermath of a global pandemic, this research is timely and crucial. It has the potential to inform health care strategies and interventions that provide targeted and holistic care to individuals grappling with long COVID. Ultimately, this study aims to improve patient outcomes, enhance the quality of life for those affected, and contribute to broader efforts to address the multifaceted health implications of this unprecedented global crisis.

## Appendix

Multimedia Appendix 1 Study clinical research form (CRF).

Multimedia Appendix 2 Ethical approval.

Multimedia Appendix 3 Informed consent form.

Multimedia Appendix 4 SPIRIT checklist.

## Abbreviations

CFQ-11: Chalder Fatigue Scale
CRF: clinical research form
DSM-III-R: Diagnostic and Statistical Manual of Mental Disorders, Third Edition, Revised
DSM-IV: Diagnostic and Statistical Manual of Mental Disorders, Fourth Edition
EQ-VAS: EuroQol Visual Analog Scale
HADS: Hospital Anxiety and Depression Scale
HRQoL: health-related quality of life
ICU: intensive care unit
MERS: Middle East respiratory syndrome
PTSD: posttraumatic stress disorder
PTSS-14: 14-item Posttraumatic Stress Scale
RT-PCR: reverse-transcription polymerase chain reaction
SARS: severe acute respiratory syndrome
SPIRIT: Standard Protocol Items: Recommendations for Interventional Trials
WHO: World Health Organization
